## Abstract

**Background:**

Patients with seasonal allergic rhinitis (SAR) frequently use homeopathic therapy. Although there is some evidence that homeopathy may be effective in treating symptoms of SAR, there is a lack of high-quality clinical trials. Therefore, the aim of the homeopathy for SAR (HOMEOSAR) trial is to determine the efficacy of individualized or standardized homeopathic drug treatment compared to placebo regarding rhinitis-related quality of life in patients with SAR.

**Methods:**

This randomized, placebo-controlled, double-blind, three-armed intervention study will be conducted at two university hospital outpatient clinics for complementary and integrative medicine in Berlin and in 12 office-based practices specializing in homeopathic treatment in Germany. A total of 270 patients with clinical symptoms of SAR and positive allergy test to birch and grass pollen will receive homeopathic anamnesis and subsequently be randomized into (a) standardized homeopathic drug treatment with Galphimia Glauca (potency D6), (b) individualized homeopathic drug treatment (D6), or (c) placebo. All three groups can receive on-demand rescue medication as needed. Treatment will consist of two consultations and daily intake of the study medication for 4 weeks during the pollen season. The primary outcome is the mean overall score of the Rhinitis Quality of Life Questionnaire (RQLQ) in weeks 3 and 4, analyzed using analysis of covariance (adjusted for baseline RQLQ overall score and study center). A closed testing procedure will be used to control the overall type I error comparing the 3 treatment groups. Secondary outcomes include the overall RQLQ and its seven domain scores, responder status (decrease in RQLQ overall score of at least 0.5 points compared to the baseline value), use of rescue medication, intensity of total and individual SAR symptoms based on visual analog scale, generic health-related quality of life, safety, utilization of health care resources and associated costs. In addition, a qualitative data analysis is planned.

**Conclusion:**

The results of our study will contribute to clarifying the possible therapeutic effects of homeopathic drug treatment for patients with SAR.

**Trial registration:**

This study has been registered in the German Clinical Trial Registry with trial ID DRKS00018081 on June 09, 2020.

## Background

Seasonal and perennial allergic rhinitis (AR) is a global health problem with a prevalence between 10 and 40% worldwide, affecting 2% to 25% of children and up to 40% of adults [1]. In Western Europe, the yearly prevalence of AR is 23% [2]. For Europe as a whole, the direct costs of AR have been estimated at 1.0 to 1.5 billion Euro, and its indirect costs have been estimated at 1.0 to 2.0 Euro billion annually [3].

Specific immunotherapy, the only causal treatment currently approved for seasonal allergic rhinitis (SAR), is time-consuming, costly, and not effective in all SAR patients [4]. Other available pharmacological treatments aiming to reduce the intensity of symptoms do not always achieve clinically relevant reductions and may cause considerable side effects. Consequently, a large number of AR patients turn to complementary medical treatments, particularly homeopathy [5–7].

In an observational study of 3,981 patients conducted in Germany and Switzerland, AR was one of the most frequent reasons why patients sought homeopathic treatment and the most common diagnosis in men who underwent classical homeopathic therapy [8].

In several trials, homeopathy has been implemented in the treatment of AR [9–17]; however, the evidence of its efficacy remains unclear. The best evidence for the efficacy of acute AR treatment is available for the homeopathic drug Galphimia glauca in decimal- (D-) potencies. A meta-analysis that included 11 studies with more than 1,000 patients demonstrated a stable therapeutic effect and a statistically significant superiority of Galphimia glauca over placebo. The clinical effect was described by the authors as being comparable to that of conventional antihistamines. Of note, all studies in the meta-analysis were conducted by the same research group [18, 19].

The most common homeopathic treatment strategy is individualized classical homeopathy. To date, the only studies that have investigated the efficacy of this treatment strategy for AR have been observational, with a high risk of selection bias, rather than randomized and placebo controlled. Nonetheless, a prospective observational study of 40 patients with atopic diseases, including AR, both seasonal and perennial allergic conjunctivitis, asthma, and neurodermatitis found clinically relevant benefits from individualized homeopathy in a prepost comparison. Furthermore, treatment satisfaction was rated as very high, and all but one patient desired to continue the therapy [17]. In another observational study with 46 patients, the prepost comparison of the disease-specific quality of life also suggested a clear improvement of SAR symptoms when treated with individual homeopathy [11].

In 2017, a systematic review with meta-analysis of studies on homeopathy in the treatment of seasonal or perennial AR was published [18, 19]. Of the 11 included studies, eight had a high risk of bias according to the Cochrane criteria. Only three studies using Galphimia glauca as an intervention were included in the meta-analysis. Regarding nasal and ocular symptoms, these studies showed efficacy in favor of homeopathy compared to placebo [20]. The authors of the systematic review concluded that, due to the heterogeneous methodological quality of the studies, any definitive assessment of homeopathic drug efficacy is questionable. They indicated that well-conducted randomized controlled trials (RCTs), which surpass identified methodological problems, are strongly required before definite conclusions on the efficacy of homeopathy for SAR can be drawn. Given the limitations of the evidence and the weak study methodology of hitherto published studies, homeopathy is not included in current national German treatment guidelines for AR. Indeed, the current AWMF (the Association of the Scientific Medical Societies in Germany) guideline states that “the effectiveness of homeopathy cannot be conclusively assessed due to the limited data available” [21]. Given that the effectiveness of homeopathy for AR has not been studied exhaustively yet, further research adhering to the highest methodological standards is needed.

### Aims

We aim to assess the efficacy of a 4-week course of i) standardized drug treatment with homeopathic preparations of Galphimia glauca or ii) an individualized homeopathic low potency drug compared to placebo with regard to disease-specific quality of life in patients with SAR.

## Methods

### Study design

HOMEOSAR (Homeopathy for Seasonal Allergic Rhinitis**)** is a three-armed, phase IV, randomized, parallel group, placebo-controlled, double blind, multicenter interventional trial for patients suffering from SAR. The study will be conducted for 8 weeks per patient, including a treatment phase of 4 weeks and a follow-up observational phase of 4 weeks (Fig. 1). By including a qualitative component, the study will follow a mixed methods approach. The Recommendations for Interventional Trials (SPIRIT) 2013 [22, 23] were also followed in the design of this trial.

**Fig. 1 Fig1:**
[figure not shown]
Design of the HOMEOSAR study. Abbreviations: *D*  Decimal potency. On-demand rescue medication consists of the oral antihistamine cetirizine (10 or 20 mg) plus, or only, if necessary, oral cortisone

### Patients and recruitment

A total of 270 patients aged 18 to 75 years and diagnosed with moderate to severe SAR will be included in the trial. The inclusion criteria consist of a skin prick test and/or a Radio-Allergo-Sorbent Test (RAST) positive for both birch and grass pollen, a score between 40 and 80 mm on a visual analog scale (VAS) for the average intensity of SAR symptoms in the week prior to inclusion, an indication for the use of oral antihistamines as anti-allergic medication, and written informed consent.

The exclusion criteria include perennial allergic rhinitis or other types of chronic rhinitis; history of anaphylactic reactions; moderate to severe atopic dermatitis; and symptoms of asthma in accordance with the GINA criteria with more than one of the following: (1) occurrence of asthma symptoms more than twice per week, (2) any night waking due to asthma, (3) reliever (beta-2-sympathomimetic drug) needed more than twice per week, except for reliever taken before exercise, (4) activity limitation due to asthma. Further exclusion criteria are renal insufficiency (serum creatinine concentration above 0.6–1.4 mg/dl or 50–130 μmol/l) measured within the last 16 weeks; current daily use of topical or systemic corticosteroids; known hypersensitivity to Galphimia glauca or other homeopathic drugs; allergen-specific immunotherapy used currently or within the past 3 years; homeopathic therapy used currently or within the past 6 weeks; a current or recent (the past 6 weeks) use of other complementary and integrative medicine treatments for SAR; alcohol addiction; pregnancy or breastfeeding; serious acute or chronic organic diseases or serious mental disorder; an acute infection with SARS-CoV-2 virus, long-COVID-syndrome, or a positive SARS-CoV-2 PCR or Rapid Antigen Test obtained 24 h prior to the baseline and/or at the 2-week follow-up visit.

For the qualitative part of the study, semistructured interviews with about 15 randomly selected study participants will be conducted.

The recruitment of study participants will be carried out primarily by advertising on public transport, in newspapers, and through flyers at general practitioners’ clinics.

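### The renal exclusion is set above a range rather than a cut-off, and its two upper limits differ: 1.4 mg/dl is 124 μmol/l, not 130

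*Protocol article*

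**What the plan says.** The exclusion criteria in the protocol article (Methods, Patients and recruitment) include "renal insufficiency (serum creatinine concentration above 0.6–1.4 mg/dl or 50–130 μmol/l) measured within the last 16 weeks". Two ranges are given, one per unit and joined by *or*, and the word *above* stands before both.

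No other section restates the criterion, gives a single threshold or says which unit governs. The Discussion lists the eligibility changes made after the first recruitment phase, and the renal criterion is not among them.

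**The concern.** There are two faults in one line.

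- **The form.** An exclusion needs one cut-off. Read literally, a value above the lower end of the range would exclude people who lie inside the range that the sentence itself gives. The workable reading is above the upper end, but the reader has to supply it.
- **The values.** On that reading, the upper limits in mg/dl and μmol/l should be the same concentration, and they are not.

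What is at stake is consistent application of an eligibility rule. The trial runs at two university outpatient clinics and 12 practices, and creatinine values up to 16 weeks old are accepted. A borderline patient could be enrolled at a site that checks μmol/l and refused at one that checks mg/dl. A secondary question concerns the per-protocol population, which is limited to patients without major protocol deviations. If an eligibility breach counts as major (the article does not say), a patient in the gap between the limits could be classified either way.

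**Working it through.** **Inputs**

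- Limits in mg/dl (Patients and recruitment): 0.6 and 1.4.
- Limits in μmol/l (same sentence): 50 and 130.
- Conversion: μmol/l = mg/dl × 10,000 / molar mass of creatinine. The molar mass is not in the article. Assuming 113.12 g/mol gives 10,000 / 113.12 = 88.4 μmol/l per mg/dl. Molar masses from 113.1 to 113.2 give factors of 88.3 to 88.4.

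**Does the plan's own pair of limits reproduce?**

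| Limit | Stated in mg/dl | × 88.4 | Stated in μmol/l | Agreement |
|---|---|---|---|---|
| Lower | 0.6 | 53.0 | 50 | yes, to the nearest 10 |
| Upper | 1.4 | 123.8 | 130 | no |

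In the other direction, 130 / 88.4 = 1.471 mg/dl. Only the upper limits disagree, and these are the ones that decide eligibility.

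**Can rounding explain it?**

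- 123.8 rounds to 124, or to 120 at the nearest 10; neither is 130.
- 1.471 rounds to 1.5 at one decimal, not to 1.4.
- The largest value that still rounds to 1.4 is about 1.449 mg/dl, and 1.449 × 88.4 = 128.1 μmol/l, still short of 130.
- A rounded factor of 88 gives 1.4 × 88 = 123.2, and 90 gives 1.4 × 90 = 126.0. Equating the two limits would need 130 / 1.4 = 92.9.

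**Size of the gap**

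- 1.471 − 1.4 = 0.071 mg/dl.
- 130 − 123.8 = 6.2 μmol/l.
- 130 / 123.8 = 1.05, so the looser limit is 5% higher.

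**Which reported values are classified differently?** The reporting precision is not given, so three assumptions are shown.

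| Assumed reporting | Discordant values | Check |
|---|---|---|
| mg/dl, one decimal | none | 1.4 passes both limits; 1.5 × 88.4 = 132.6 fails both |
| mg/dl, two decimals | 1.41 to 1.47 (seven) | 1.47 × 88.4 = 129.9 passes 130; 1.48 × 88.4 = 130.8 fails |
| μmol/l, whole numbers | 124 to 130 (seven) | 123 / 88.4 = 1.391 passes 1.4; 124 / 88.4 = 1.403 fails |

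**Does the word *or* settle it?** If exceeding either limit excludes, 1.4 mg/dl always governs and 130 μmol/l is a figure that never decides a case. If a site checks only the unit its laboratory reports, the unit decides for every patient in the gap. Either way, the line as printed contains a number that does not do its job.

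**The case against.** The conversion is not in dispute; the case against is that the point is trivial. A physician would read the criterion as above the normal range. The two ranges look like separately rounded reference intervals, and the sentence does not claim that they are equal. If either limit excludes, the rule is unambiguous. With creatinine in mg/dl to one decimal, the precision in which that limit is written, no value is discordant. The separate exclusion of serious organic disease would catch serious kidney disease in any unit. The article gives no reason for the renal exclusion, so it cannot be assumed that 124 to 130 μmol/l carries more risk. It also condenses a full protocol that may state a working cut-off, and tightening a criterion during recruitment means an amendment.

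Much of this stands as a limit on importance. The wording fault alone would be editorial, the number of patients affected may be zero, and no between-arm bias follows.

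It does not remove the error. Rounding does not turn 124 into 130. Reading *or* as either limit rescues the rule only by making one printed figure inert, and that figure misleads anyone checking in μmol/l. The exclusion of serious disease does not settle a mildly raised value. Nor is this an omission that a fuller document would fill: the article states two limits, and they conflict.

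**Conclusion.** The concern holds: the criterion is wrong as written. It puts *above* before a range, and its two upper limits differ by 6.2 μmol/l (0.07 mg/dl, 5%). The only outside input is the conversion factor, a physical constant, and every plausible value gives the same conclusion.

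The practical effect is small. Depending on how creatinine is reported, between zero and seven reportable values are discordant. The article does not show which unit the sites use or that any patient was classified differently. Eligibility is decided before randomization, and the primary analysis covers all randomized patients as allocated, so sample size, power, type I error and the primary comparison are unaffected. This is a correction worth making, not a threat to the trial's conclusions.

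**What to change.** Replace both ranges with one upper cut-off and its equivalent: serum creatinine above 1.4 mg/dl (124 μmol/l; exact conversion 123.8). The stricter limit is preferable because it already governs if either limit excludes. Name mg/dl as the governing unit, since a reading of exactly 124 μmol/l is 1.403 mg/dl and would otherwise sit on the boundary. Use the same figure in the case report form.

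The text change is one line in each document. If recruitment is still open, it also needs an amendment, and it costs at most the few patients at 124 to 130 μmol/l who would have passed on the μmol/l limit alone. The sample size does not change.

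The Trial status section expects recruitment and data collection to end by October 2023. If enrollment is complete, state in the results report which limit was applied and check whether any enrolled patient had a value between 124 and 130 μmol/l.

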### Study physicians

This multicenter RCT will be conducted at two outpatient clinics for complementary and integrative medicine located at the university hospital in Berlin (Charité – Universitätsmedizin Berlin) and at 12 family medicine clinics specialized in homeopathic treatment located in the Berlin and Munich metropolitan areas, Germany. The study physicians are medical doctors required to hold certifications for medical specialists, e.g., general medicine (German: “Facharztbezeichnung”) and an additional qualification for homeopathy (German: “Zusatzbezeichnung Homöopathie”), as well as at least five years of practical experience in providing homeopathic treatment.

### Study procedures

The study will be conducted during the birch and/or grass pollen season (this is usually between February and the end of July in Germany). After providing written informed consent, all patients included in the study will receive a baseline assessment, rescue medication, and subsequently a first homeopathic consultation of 60 to 120 min. After the consultation, study physicians will prescribe an individualized homeopathic drug. The prescription will then be sent by fax to the study pharmacy, where the patient will be randomized into one of the two homeopathic drug treatment groups and the placebo group and obtain his or her allocated study medication for the duration of the study.

In case of need, patients in all groups are allowed to take predefined rescue medication and will be instructed to document the daily applied rescue medication in the medication diary between baseline and the end of week 4, as well as in weeks 7 and 8. Furthermore, the dosage of the study medication will be documented daily between baseline and the end of week 4. Additional patient questionnaires will be distributed to patients at baseline and sent directly to patients by the study administration center at the end of weeks 2, 4, and 8. These questionnaires will consist of the Rhinitis Quality of Life Questionnaire (RQLQ); a visual analog scale measuring symptom intensity of SAR; a questionnaire on generic health-related quality of life (SF-12); as well as questions concerning the severity of asthma and atopic eczema, health care resource utilization, and expectations and assumptions regarding treatment group allocation.

After the 4-week treatment phase, the patient will be instructed to hand any remaining study medication and the original packets of the rescue medication back to the investigators in a pre-postaged return envelope.

### Intervention and rescue medication

After randomization by the study pharmacy, patients will receive either the registered homeopathic drug Galphimia glauca in potency D6, an individualized and registered homeopathic drug selected by the study physician in potency D6, or the placebo treatment. All patients will receive their study medication as alcoholic dilution in identical bottles and start treatment within 5 days after the first consultation. The standard dose is five drops of the assigned study drug taken orally three times a day. The prescribed drug dosage can be individually adjusted (i.e., increased or decreased) by the study physician, in accordance with the established homeopathic treatment principles. Patients will also be advised to store the medication in a dark place at room temperature, separate from other drugs, and to shake the bottle strongly ten times according to homeopathic recommendations prior to taking the medication. The second homeopathic consultation (duration of a maximum of 30 min) will be conducted for all patients approximately 14 days after the first homeopathic consultation. Although study physicians may prescribe another individualized homeopathic drug to each patient after two weeks, only those randomized to the individualized homeopathic treatment group will receive the changed homeopathic drug. Patients in the other two treatment groups will continue to receive standardized treatment (Galphimia glauca D6) or placebo.

Galphimia glauca D6 and all individualized homeopathic products with a potency of D6 are registered and routinely used medicinal products in Germany. They are available as “over the counter” drugs in any German pharmacy and are registered by a positive monograph from Commission D (German: Kommission D) of the Federal Institute for Drugs and Medical Devices (BfArM). In the individualized homeopathic drug treatment arm, any homeopathic medicinal product that is registered, monographed, and available from “Deutsche Homöopathie-Union” (manufacturers of homeopathic medicinal products) can be prescribed.

Patients in all treatment groups may take second-generation oral antihistamines (10 or 20 mg cetirizine) on demand as rescue medication. In case when a daily maximum dose of 20 mg cetirizine is not sufficiently effective, patients may additionally take an oral cortisone preparation (max. prednisolone 10 mg/day). During the 8-week study period, patients are asked not to use any concomitant homeopathic treatment or any other complementary and integrative medical treatments (e.g., herbal medicine, acupuncture, and others) for the treatment of SAR symptoms.

### Outcome measures

The primary outcome is disease-related quality of life (RQLQ, Fig. 2). To allow enough time to assess the drug effect and to have a broad time window to compensate for weekly fluctuations in pollen flow and SAR symptoms, the RQLQ mean of weeks 3 and 4 was chosen as the primary outcome (Fig. 3).

**Fig. 2 Fig2:**
[figure not shown]
Data collection time points of primary and secondary outcome measures. Abbreviations: *RQLQ*  Rhinitis Quality of Life Questionnaire, *VAS SAR*  Visual analog scale of seasonal allergic rhinitis symptoms, *SF-12*  Generic health-related quality of life questionnaire Short Form 12, *TNSS*  Total Nasal Symptom Score, *RMS*  Rescue Medication Score. * Primary outcome: Mean of the two RQLQ overall scores

**Fig. 3 Fig3:**
[figure not shown]
Standard Protocol Items: Recommendations for Interventional Trials (SPIRIT) Figure. Abbreviations: *RQLQ*  Rhinitis Quality of Life Questionnaire, *VAS SAR*  Visual analog scale of seasonal allergic rhinitis symptoms, *SF-12*  Generic health-related quality of life questionnaire Short Form 12, *TNSS*  Total Nasal Symptom Score, *RMS*  Rescue Medication Scor e

The RQLQ is a well-established and validated questionnaire developed by Juniper et al. [24, 25]. It has been used successfully as a primary [15, 26–28] or secondary endpoint [29] in numerous studies of high methodological quality. The RQLQ consists of 28 questions in 7 domains, including activity limitation, sleep problems, nose symptoms, eye symptoms, other symptoms, practical problems, and emotional state, ranked from 0 (no impairment) to 6 (severe impairment). The RQLQ also captures nasal symptoms as a standard endpoint for allergic reactions [30].

Secondary outcome measures will be measured at the end of weeks 2, 3, 4, 7, and 8 and will include the RQLQ overall score and the seven RQLQ domain scores, nasal symptoms (Total Nasal Symptom Score, TNSS), the use of rescue medication (Rescue Medication Score, RMS), and SAR symptoms (nasal and nonnasal, 100 mm VAS ranging from 0 mm = no symptoms to 100 mm = max. symptoms). The responder status is defined by at least a 0.5-point decrease (improvement) in the RQLQ overall score (mean of weeks 3 and 4) compared to the baseline value. The generic health-related quality of life (SF-12) questionnaire will be used to assess the perceived homeopathic drug treatment effect on generic quality of life and to measure quality-adjusted life years (QALYs). For the health economic analysis, the patient-specific use of health care resources during the study (doctor contacts, hospital stays, medication, remedies and aids, work absence and incapacity days) will be documented continuously, and the associated costs will be calculated. Combined with the results on QALYs, a cost-effectiveness assessment of the study treatment will be carried out. Adverse events (AEs), serious adverse events (SAEs), and the number of patients who discontinue treatment due to AEs or SAEs will be collected from baseline until completion of the study.

In the qualitative part of the study, the subjective experiences of treatment, treatment satisfaction and subjectively perceived effects of the treatment will be assessed.

